#### Attrition

To allow an attrition rate of 20%–25%, the resulting total of 675 was increased to give a final sample size of 880.

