### Sample size

Sample size calculations were carried out separately for the model development and validation cohorts. For both, we used estimated prevalences for DO, BOO and DU of 57%, 31% and 16%, respectively, based on previous literature^4 5^ and clinical expertise.

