#### Development cohort

The sample size for developing our predictive models was based on a rule of thumb suggesting that five events per variable are required.^6^ We chose a sample size of 350 to allow at least 11 variables in each model. This was driven by our lowest estimated prevalence of 16% for DU, giving 56 events (DU diagnoses).

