#### Validation cohort

The sample size for the validation cohort was chosen to ensure that estimates of test accuracy are made with adequate precision. We deem sensitivity and specificity of 75% to be the minimum clinically useful performance. We chose a sample size of 325, giving estimates of sensitivity of 75% to within 8%, 10% and 14% for DO, BOO and DU respectively, based on ‘positive’ samples of 185, 101 and 52, and estimates of specificity of 75% to within 8%, 7% and 6%, based on ‘negative’ samples of 140, 224 and 273. Better sensitivity and specificity will give narrower CIs.

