## Statistical analysis

Model development will be performed using results from the first 350 data sets, and external model validation performed using the subsequent 325 data sets.

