### Missing data

Patterns of missing data will be investigated to infer the ease with which each parameter can be obtained in practice. In the event of missing data, multiple imputation by chained equations^8^ will be used to impute missing values to avoid bias and make best use of the data.

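### Minor: 880 enrolled gives 675 data sets only up to 23.3% attrition, so the top of the 20%–25% allowance is not met; validation should use all data sets after the first 350

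*Protocol article*

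**What the plan says.** The article sizes its two cohorts separately. Under Development cohort: "We chose a sample size of 350 to allow at least 11 variables in each model". Under Validation cohort: "We chose a sample size of 325, giving estimates of sensitivity of 75% to within 8%, 10% and 14% for DO, BOO and DU respectively", with specificity of 75% estimated to within 8, 7 and 6 points for the same three conditions. Both calculations share one set of prevalences: "we used estimated prevalences for DO, BOO and DU of 57%, 31% and 16%, respectively".

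The sum is then inflated under Attrition: "To allow an attrition rate of 20%–25%, the resulting total of 675 was increased to give a final sample size of 880". No single rate within that range is named as the one that produced 880.

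The Statistical analysis section allocates the data sets in order: "Model development will be performed using results from the first 350 data sets, and external model validation performed using the subsequent 325 data sets". Under Missing data, gaps are to be filled by imputation: "In the event of missing data, multiple imputation by chained equations".

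**The concern.** A plan that allows for a range of attrition is normally read as still delivering its target at the top of that range. Here it does not quite do so. The order of allocation also decides where a deficit lands. Development is filled first, so validation alone runs short, and validation is the cohort that supplies the independent estimates of sensitivity and specificity, the primary outcome. Its size was justified by the precision of those estimates.

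At the other end of the range the plan yields more than 675 data sets, while the validation cohort is described by a fixed count. Within the sponsor's own range, then, 325 is either not reached or leaves some data sets without a stated role. What is at stake is a design figure that does not deliver what is said of it, and a cohort definition that leaves a decision open until after recruitment.

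**Working it through.** **Inputs.** Development 350, validation 325, total 675, attrition 20%–25%, enrolment 880, prevalences 57% (DO), 31% (BOO) and 16% (DU). All come from the Sample size and Statistical analysis sections.

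**Reproducing 880.** The inflation formula is N = n/(1 − d), rounded up.
- d = 20%: 675/0.80 = 843.75, so 844
- d = 22.5%: 675/0.775 = 870.97, so 871
- d = 25%: 675/0.75 = 900

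The stated 880 lies between the end-points. The mistaken form n × (1 + d) gives 810 to 844 and cannot produce 880, so the inflation was done in the right way, for a rate inside the range.

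**Break-even.** 1 − 675/880 = 0.233, that is 23.3%.

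**Ends of the range**, with the first 350 data sets going to development:
- 25%: 880 × 0.75 = 660; 675 − 660 = 15 short (2.2%); validation 660 − 350 = 310
- 20%: 880 × 0.80 = 704; 704 − 675 = 29 over; up to 704 − 350 = 354 for validation

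**Expected positives at validation n = 310.** DO 310 × 0.57 = 176.7; BOO 310 × 0.31 = 96.1; DU 310 × 0.16 = 49.6. The article's figures at 325 are 185, 101 and 52.

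**Effect on precision.** The article does not name its interval method. I used the exact (Clopper–Pearson) 95% interval at 75% and took its wider, lower arm, in percentage points.

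| Estimate | Stated | n = 325 | n = 310 |
|---|---|---|---|
| Sensitivity, DO | 8 | 6.9 | 7.1 |
| Sensitivity, BOO | 10 | 9.6 | 9.9 |
| Sensitivity, DU | 14 | 13.9 | 14.3 |
| Specificity, DO | 8 | 8.0 | 8.2 |
| Specificity, BOO | 7 | 6.2 | 6.4 |
| Specificity, DU | 6 | 5.6 | 5.7 |

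The largest change is about 0.4 points, for DU sensitivity. To the nearest whole point, no margin at 310 exceeds its stated value. Wald half-widths, 1.96 × √(0.75 × 0.25/m), where m is the number with or without the condition, are smaller for every estimate. For DU sensitivity they go from 11.8 to 12.1.

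**If all 354 were used at 20% attrition.** DU positives would be 354 × 0.16 = 56.6, and the exact lower margin for DU sensitivity would fall from 13.9 to about 13.3 points.

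**Development cohort.** It keeps its 350 data sets and 350 × 0.16 = 56 expected DU events at either end of the range.

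**The case against.** The strongest reply is that 880 is a reasonable rounded planning figure. It lies inside the 844 to 900 that the range implies, above the size for the midpoint (871), and covers attrition from 20% to 23.3%, about two thirds of the range. What counts as attrition is not defined. Since missing values are to be imputed, a man with some missing results need not be lost as a data set. The sponsor may also recruit until 675 data sets are in hand, in which case neither shortfall nor surplus arises.

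Most of this stands. It shows that the sample size is not wrong in kind and that the harm is slight. It does not make the sentence accurate: a figure between the two end-points cannot cover the upper one, and nothing in the article says that 880 was meant for a lower rate.

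Two stronger readings are tempting, and the article supports neither. A reader might infer that the validation cohort, and with it the primary outcome, is materially underpowered at 25% attrition; the table in the working shows otherwise. A reader might also infer that surplus data would be thrown away. The article gives the validation set as "external model validation performed using the subsequent 325 data sets", which repeats the planned target. It nowhere says that later data sets are excluded, and the full protocol or analysis plan, not shown, may settle the matter.

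**Conclusion.** The point holds as a minor one. The stated enrolment meets the stated attrition allowance up to 23.3% and not up to 25%, where it is 15 data sets short. As the allocation is written, all 15 come out of validation. The cost in precision is at most about 0.4 points on any margin and moves none of them past its stated value at the precision the article reports. Below 23.3% attrition the fixed count leaves the role of the extra data sets unstated, up to 29 of them at 20%.

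This assumes that all 880 men are enrolled, that attrition means loss of a whole data set, that the article's prevalences hold, and that exact 95% intervals are a fair guide to the stated margins.

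**What to change.** Change two sentences.

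1. Under Attrition, say that enrolling 880 allows attrition of up to about 23%, and that at 25% the validation cohort would be about 310. Enrolling 900 would cover 25% in full, 20 more men (2.3%), but the small loss of precision does not call for it.
2. Under Statistical analysis, define the validation cohort as all data sets after the first 350, with a target of 325 and about 310 to 354 expected over 25% to 20% attrition.

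The first corrects a stated design figure; its only cost is a slightly less generous allowance. The second leaves no data set outside both cohorts, gains a little precision if attrition is low, and settles membership of the validation cohort before its data are analysed. Neither needs extra men. If the full protocol or analysis plan already settles either point, the article need only be brought into line with it.

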## Statistical analysis

Model development will be performed using results from the first 350 data sets, and external model validation performed using the subsequent 325 data sets.

### Model development

Candidate predictor variables will be selected from those listed in table 1. Their selection has been informed by subject knowledge using literature review and expert judgement. As predictor distributions should be wide to facilitate reliable predictions, we will explore the distribution of each predictor prior to selection. Relationships between predictors will also be investigated; where indicated we will group related variables into a composite variable or exclude if highly correlated with other variables. Candidate predictors will not be selected based on univariable analyses; this practice is discouraged because predictors that may be important in a multivariable model can be missed and may also lead to overoptimistic models. Therefore, all selected candidate predictor variables will be included in the multivariable logistic regression models without evaluation of association between outcome and predictor and assessment of statistical significance. To gain maximum diagnostic information, continuous variables will not be categorised. We will allow for non-linearity by using a multivariable fractional polynomial approach to identify appropriate transformations. This may lead to the inclusion of non-linear terms in the models, thus increasing the number of variables in the models. Using multiply imputed data and Rubin’s rule, we will develop each model using backward elimination with a p value of 0.157 to select predictors for inclusion in each model. We chose this p value because it is known to be a good proxy for the Akaike information criterion approach. If the repeated use of Rubin’s rule is computationally challenging, we will use the approximation to Rubin’s rule recommended by Wood *et al*.^7^

### Model validation

The predictive performance of each model will be assessed in terms of discrimination, that is the ability to distinguish between those who do or do not have a particular diagnosis, and calibration meaning agreement between predicted and observed probabilities. Discriminative ability will be assessed using the c-index and its 95% CIs. For a logistic model, this is equivalent to the area under the Receiver Operator Characteristic (ROC) curve. Calibration will be evaluated in two ways. Calibration plots of average observed probability against predicted probability will be used to visually assess calibration. Within each quintile or decile of predicted probability (depending on the distribution of data), the average predicted probability will be compared with the corresponding observed proportions. We will also quantify calibration by estimating the calibration slope of the prognostic index (linear predictor) using logistic regression with the linear predictor as the covariate.

The apparent c-index and calibration slope will be estimated for each model. Bootstrapping will be used for internal validation to assess model overfitting and optimism. For each model, we will obtain 100 bootstrap samples from each imputed data set and repeat the variable selection process. The optimism is the difference between the c-index from the bootstrap sample and that from the original imputed data set. The average optimism will be determined across bootstrap samples and imputed data sets, and the optimism-adjusted c-index will be calculated by subtracting the average optimism from the apparent c-index of the original model. Similarly, we will obtain the optimism-adjusted calibration slope. The optimism-adjusted calibration slope will be used as the uniform shrinkage factor to correct a model.

We will externally validate the models and calculate performance statistics (c-index and calibration slope) using the validation cohort. The value for the calibration slope should ideally be one signifying perfect agreement between the predicted probabilities and the observed probabilities. A calibration slope <1 indicates that a model overpredicts while a calibration slope >1 indicates underprediction. From the qualitative research, we will ascertain distributions of probability (risk) thresholds for clinical usefulness of the prediction in guiding treatment of each condition. The sensitivity and specificity (and their corresponding 95% CIs) will be calculated for these risk thresholds and plotted on an ROC plot for each model.

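### The plotted calibration check compares quintile or decile averages; with 325 men and about 52 DU cases, a prespecified smooth curve would estimate risk more precisely from the same data

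*Protocol article*

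**What the plan says.** The protocol article (Statistical analysis, Model validation) states that "Calibration will be evaluated in two ways". The first way is graphical: "Calibration plots of average observed probability against predicted probability will be used to visually assess calibration". The comparison behind the plot is grouped: "Within each quintile or decile of predicted probability (depending on the distribution of data), the average predicted probability will be compared" with the observed proportion in the same group.

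The second way does not use groups. It is the calibration slope, from a logistic regression of the diagnosis on the linear predictor. For external validation the section names the c-index and the calibration slope as the performance statistics. It reads a slope below 1 as overprediction and a slope above 1 as underprediction. No other calibration statistic and no smooth calibration curve is mentioned.

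Under Sample size, the validation cohort is fixed ("We chose a sample size of 325") with "estimated prevalences for DO, BOO and DU of 57%, 31% and 16%, respectively". Its precision for sensitivity is "based on ‘positive’ samples of 185, 101 and 52".

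**The concern.** The models output a probability for each condition. Those probabilities are to be linked to management recommendations, with risk thresholds elicited in the qualitative work. Whether a stated risk is close to the true risk near such a threshold is therefore a central question for external validation.

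A group average answers it poorly. Each plotted point uses only a fifth or a tenth of the men, its position depends on where the cuts fall, and it describes a range of risk, not the risk at a threshold. The slope does not fill the gap. It measures whether predictions are too extreme or too moderate. A model that is too high or too low by the same amount on the logit scale throughout still has a slope near 1, even though the protocol describes the slope in terms of over- and underprediction. Among the stated calibration measures, the plot is thus the only one that can show a uniform shift and the main one for curvature.

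**Working it through.** **Inputs from the protocol article.** Validation cohort 325; prevalences DO (detrusor overactivity) 57%, BOO (bladder outlet obstruction) 31%, DU 16%; 5 or 10 groups.

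**Reproducing the plan's own figures.** Events = N × prevalence: 325 × 0.57 = 185.25, 325 × 0.31 = 100.75, 325 × 0.16 = 52.0. These match the stated "samples of 185, 101 and 52".

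**Precision of one plotted point.** With g groups, m = 325/g men per group: 65 per quintile, 32.5 per decile. The 95% half-width is 1.96 × √(p(1 − p)/m), evaluated at p = overall prevalence.

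| | Events per quintile | Half-width, quintile | Events per decile | Half-width, decile |
|---|---|---|---|---|
| DU, p = 0.16 | 52/5 = 10.4 | 1.96 × √(0.1344/65) = 8.9 points | 5.2 | 1.96 × √(0.1344/32.5) = 12.6 points |
| BOO, p = 0.31 | 101/5 = 20.2 | 1.96 × √(0.2139/65) = 11.2 points | 10.1 | 1.96 × √(0.2139/32.5) = 15.9 points |
| DO, p = 0.57 | 185/5 = 37.0 | 1.96 × √(0.2451/65) = 12.0 points | 18.5 | 1.96 × √(0.2451/32.5) = 17.0 points |

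The exact interval for 5 DU cases among 32 men runs from 5% to 33%. DU has the fewest events, but in absolute terms the points for BOO and DO are no more precise, so the issue applies to all three models.

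**Error in the estimated risk (simulation).** The documents give no spread of predicted risk, so one is assumed: a normal linear predictor with SD 0.77, 1.02 or 1.33, giving a c-index of about 0.70, 0.75 or 0.80. Cohorts of 325 were simulated, 200 to 400 per scenario, with the truth perfectly calibrated, of slope 0.7, of slope 0.5, or curved. Grouped proportions were compared with a loess curve (span 0.75 or 0.5) and a 3-knot restricted cubic spline logistic curve, all averaged over the same groups. The criterion was the root-mean-square error (RMSE) against the true risk.

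- DU, quintiles: grouped RMSE 3.6–4.4 points. Loess with span 0.75 was 21–28% lower, loess with span 0.5 17–23% lower, the spline 24–30% lower.
- DU, deciles: grouped RMSE 5.2–6.2 points. The reductions were 34–45%, 32–40% and 44–49%.
- BOO and DO: about 19–36% lower than quintiles and 33–54% lower than deciles.

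Over all three conditions the reduction is 17–36% against quintiles and 32–54% against deciles.

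**How often miscalibration is detected, DU.** A 5% test on the groups stands in for reading the plot by eye. Where three figures are given, they are for c-index 0.70/0.75/0.80.

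| True miscalibration | Quintiles | Deciles | Spline curve | Calibration slope |
|---|---|---|---|---|
| Slope 0.7 | 29/47/65% | 25/42/62% | 36/62/82% | 44/58/71% |
| Uniform shift of +0.5 logit | 51–63% | 32–39% | 75–82% | 3–6% |
| Curved | 18–39% (either grouping) | 18–39% (either grouping) | 51–74% | 26–30% |

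For a uniform shift, the slope's detection rate is about what a 5% test gives by chance. With a true slope of 0.5, groups detect the problem in 96–100% of runs, as the other methods do. Choosing deciles over quintiles costs a good part of the ability to see a shift, and the protocol leaves that choice open.

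**The case against.** The case on the other side is substantial, and much of it stands.

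- A reader might infer that calibration is judged on groups alone. It is not: the ungrouped slope is planned and is one of the two statistics named for external validation. At a true slope of 0.7 and a c-index of 0.70 it detects more (44%) than the spline curve (36%).
- A reader might infer that groups are too noisy to show any miscalibration. They are not: gross overfitting shows almost always. Nor is a near-empty lowest DU decile damning in itself. About 0.8 expected events in 32.5 men (p about 0.025) gives a standard error of √(0.025 × 0.975/32.5) = 2.7 points, well below the error in an average decile.
- A reader might see a conflict with the rule under Model development against categorising continuous variables. That rule concerns predictors entered in the models; grouping predicted risks for a display does not breach it.
- A reader might suspect that the analyst could pick the more flattering grouping. The wording most naturally refers to the distribution of the predicted risks, and nothing says that the outcomes or the look of the plot decide. The flexibility also lets the team use quintiles where data are sparse.
- The primary outcome is sensitivity and specificity. The cohort was sized for those, and both are to be reported with intervals at the elicited thresholds.
- A journal article leaves plotting detail to the analysis plan, and this text does not exclude a smooth overlay.

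The last two points limit the weight of the concern but do not remove it. Sensitivity and specificity at a threshold do not show whether the risk stated there is right. The article also does not leave the method open: it names the grouped comparison, and a better one exists for the same data.

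**Conclusion.** The point holds in limited form. Apart from the slope, the only stated calibration check is a comparison of group averages, with the number of groups left to the data. At 325 men it is imprecise for all three conditions: for DU, about ±8.9 points per quintile and ±12.6 per decile at a risk of 16%. It often misses moderate miscalibration, a uniform shift or curvature, and the slope is nearly blind to the shift.

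A smooth curve lowers the error in estimated risk by roughly 17–36% against quintiles and 32–54% against deciles. These percentages depend on the assumed normal linear predictor, a c-index of 0.70 to 0.80, the smoother, and the shapes of miscalibration simulated; the low end belongs to quintiles. The detection rates rest on the same assumptions, were obtained for DU only, and use a formal test in place of a visual reading.

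This is a cheap improvement to a descriptive display. Nothing in the documents makes the planned validation invalid.

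**What to change.** For each of the three models, define the calibration plot as a flexible curve: the observed diagnosis regressed on a restricted cubic spline (or loess) of the linear predictor, with a 95% band. Fix the number and position of knots, or the span, before the validation data are analysed. Read off the observed risk with its confidence interval at each elicited risk threshold. Keep grouped points only as an overlay, with the number of groups set in advance, and keep the calibration slope as planned.

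The cost is a change of wording and one standard plot, with no extra participants or data. There is a small downside: the smoother has to be fixed in advance and can add slight bias. For DU with a true slope of 0.5 and a c-index of 0.80, the loess gain fell to 22% against quintiles and 34% against deciles. If the statistical analysis plan already specifies such a curve, it is enough to align the protocol wording with it.

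### The bootstrap resamples data that are already imputed, so when predictors are missing it understates optimism and sets the shrinkage factor too close to 1

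*Protocol article*

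**What the plan says.** The Model development section of the protocol article builds each model on imputed data: "Using multiply imputed data and Rubin’s rule, we will develop each model using backward elimination with a p value of 0.157". An approximation to the pooling is allowed if computing is heavy, and fractional polynomials handle non-linearity. The Missing data section names chained equations as the imputation method. It gives neither an expected amount of missing data nor a number of imputations.

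The Model validation section then describes the bootstrap: "For each model, we will obtain 100 bootstrap samples from each imputed data set and repeat the variable selection process". Optimism is defined against the same completed data: "The optimism is the difference between the c-index from the bootstrap sample and that from the original imputed data set". It is then averaged: "The average optimism will be determined across bootstrap samples and imputed data sets". The slope is obtained in the same way and put to use: "The optimism-adjusted calibration slope will be used as the uniform shrinkage factor to correct a model".

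The article does not say in words whether selection in a bootstrap sample is done within one imputed data set or pooled over several. One set at a time is the natural reading, because each sample is drawn from one set.

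**The concern.** A bootstrap estimate of optimism is valid to the extent that it replays everything that was done to obtain the model. Here the model comes from three steps: impute, transform, and eliminate on pooled p values. The plan starts the replay after the first step, so filled-in values are resampled as if they had been observed.

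This makes the training and test data too alike in two ways. The imputed values in a bootstrap sample were generated from all 350 men, including those not drawn. The same values also stand in the data set in which the bootstrap model is tested. The extra overfitting that comes from missing data then hardly registers.

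More than a reported statistic is at stake. The adjusted slope multiplies the coefficients of the models before they go to the validation cohort and into the tool. A factor too near 1 leaves predictions too extreme and the adjusted c-index too favourable.

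**Working it through.** **The plan's own figures.** The article gives no figure for optimism or shrinkage. The figures around it reproduce. For the development cohort, 350 × 0.16 = 56 events, and 56/5 = 11.2, which matches the stated 11 variables at five events per variable. The elimination threshold is 2(1 − Φ(√2)) = 0.1573, the AIC equivalent for one degree of freedom.

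**Inputs from the article.** Development sample 350 and 12 candidate parameters (Index tests); prevalence 16% for DU and 57% for DO (Sample size); elimination at 0.157 with Rubin's rule; chained equations.

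**Assumptions.** Correlation 0.3 between predictors; values missing completely at random at the same rate in every predictor; 5 imputations with the outcome included; coefficients giving a true c-index of about 0.70 to 0.72; fewer bootstrap samples than planned (100 in total for the plan's scheme, 40 for each alternative). There were 120 replicates at 16% prevalence and 100 at 57%. Fractional polynomials were not simulated.

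**Schemes compared.**
- Plan: impute, resample each completed set, select within that set.
- Half-fix: impute, resample the same men in all completed sets, select by Rubin's rule.
- Full fix: resample the incomplete data, impute again, select by Rubin's rule.
- True: the final pooled model applied to 20,000 new complete records.

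Shrinkage factor = apparent slope − mean optimism in the slope.

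**Results at 16% prevalence.**

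| Missing in every predictor | c-index optimism: plan / full fix / true | Factor: plan / half-fix / full fix | True slope | Plan − full fix |
|---|---|---|---|---|
| 0% | 0.048 / 0.049 / 0.053 | 0.778 / 0.776 / 0.775 | 0.751 | 0.003 |
| 5% | 0.048 / 0.050 / 0.056 | 0.777 / 0.789 / 0.768 | 0.740 | 0.009 |
| 10% | 0.047 / 0.052 / 0.060 | 0.780 / 0.807 / 0.760 | 0.723 | 0.020 |
| 20% | 0.046 / 0.059 / 0.067 | 0.782 / 0.832 / 0.734 | 0.702 | 0.048 |
| 30% | 0.044 / 0.068 / 0.077 | 0.787 / 0.856 / 0.698 | 0.666 | 0.089 |

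Standard errors are at most 0.0012 for the bootstrap optimism estimates, 0.0037 for true optimism and 0.014 for the true slope.

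As missingness rises, true optimism rises but the plan's estimate drifts down, and its factor stays at 0.78 to 0.79. The full fix moves in the right direction.

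**At 57% prevalence.** The factor under the plan and the full fix is 0.842 and 0.846 with complete data, 0.843 and 0.824 at 10% missing, and 0.841 and 0.796 at 20%. The true slopes are 0.811, 0.793 and 0.774.

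**Separating the two features (16% prevalence, 20% missing).** Resampling completed data with pooled selection gives optimism 0.035 and factor 0.83. Changing only to single-set selection raises optimism to 0.046 and lowers the factor to 0.78. Single-set selection keeps more variables (5.9 on average, against 4.9 under the full fix), so it works against the bias.

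**A second simulation** used uneven assumed missingness: 25% for the four Flowtaker inputs, 12.5% for diary inputs and 6% for one other. For DU with a true c-index of 0.77, the factor was 0.78 under the plan and 0.75 under the fix (true slope 0.73). For a weaker DU model (true c-index 0.69) it was 0.71 and 0.67 (true 0.60). For BOO it was 0.83 and 0.80 (true 0.80).

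**The case against.** Several objections have force.

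- **Single-set selection.** A reader might infer that selecting within one imputed set, out of line with the pooled rule in Model development, also causes optimism to be understated. The article does not state that reading, and the separation above shows the opposite effect: it partly offsets the bias. The mismatch is real, but it is not the cause.
- **Amount of missing data.** No rate is given, and imputation is planned only if data are missing. The 20%–25% under Attrition concerns recruiting 880 to obtain 675 and gives no support for that rate within the first 350 data sets. This stands, so the size can only be shown as a range. Missing data are nevertheless foreseen: the article's limitations mention tests that may be missing, and the diary and Flowtaker are used at home.
- **Gap to the truth.** A reader might charge the whole gap between planned factor and true slope to this feature. That is not supported. Some remains under the full fix, and some exists with complete data (0.78 against 0.75). Only the difference between plan and fix counts.
- **DU hit hardest.** This is barely supported. At 20% missing the difference is 0.048 at 16% prevalence and 0.841 − 0.796 = 0.045 at 57%.
- **Practical effect.** With a normal linear predictor and a re-estimated intercept at 16% prevalence, moving the factor from 0.78 to 0.75, or from 0.71 to 0.67, shifts predicted probabilities by 0.3 to 0.5 percentage points on average, and by at most 1.7 at the 95th percentile. The sampling standard error of a calibration slope in 325 men is about 0.17 to 0.23. This stands for differences of that size.
- **External validation.** The separate cohort would reveal leftover under-shrinkage. It would not prevent it, because the factor is set beforehand and the article states no recalibration step.

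It could also be said that a condensed article leaves such detail to the analysis plan. That fails here, because the order of imputation and resampling is stated outright.

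**Conclusion.** The point holds in limited form. Resampling completed data omits the imputation step from internal validation. When predictors are missing, it understates optimism and gives a uniform shrinkage factor too close to 1. Against the full fix at 16% prevalence, the excess is about 0.01 at 5% missing in every predictor, 0.02 to 0.03 at 10%, 0.05 at 20% and 0.09 at 30%. It is nil with complete data. These sizes rest on assumed missingness, correlation and number of imputations, and on simulations without fractional polynomials.

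Severity is minor to moderate. Uniform shrinkage leaves the ranking of men, the ROC curve and the validation c-index as they are. It changes predicted probabilities, and so sensitivity and specificity at fixed risk thresholds. The documents do not support a claim that the primary accuracy estimates are invalid, since those are made in a separate cohort.

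**What to change.** Reverse the order in the Model validation section:

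1. Draw bootstrap samples from the incomplete development data of 350 men.
2. In each sample, repeat the imputation, the fractional-polynomial step and the pooled backward elimination described under Model development.
3. Test each resulting model in the imputed original data, and average the differences in c-index and slope.
4. Use the resulting optimism-adjusted slope as the uniform shrinkage factor.

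Do not change the selection step alone. Pooled selection on data already imputed moves the factor further from the truth (0.83 instead of 0.78 at 20% missing, with a true slope of 0.70).

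If computing is heavy, use few imputations per bootstrap sample together with the approximation to Rubin's rule that the article already permits.

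The cost is a change of wording, more computing time, and a slightly less favourable adjusted c-index and slope. No new data or participants are needed. Some optimism will remain uncorrected, so the calibration slope in the validation cohort should still be read as the main check.
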